## PROTOCOL SYNOPSIS

|                                                                |                                                                                                                                                                                                                                                                                                                                                                                                                                                                                                                                                                                                                                                                                                                                                                                                                                                                                                                                                                                                                                                                                                                                                                                                                                                                                                |
|----------------------------------------------------------------|------------------------------------------------------------------------------------------------------------------------------------------------------------------------------------------------------------------------------------------------------------------------------------------------------------------------------------------------------------------------------------------------------------------------------------------------------------------------------------------------------------------------------------------------------------------------------------------------------------------------------------------------------------------------------------------------------------------------------------------------------------------------------------------------------------------------------------------------------------------------------------------------------------------------------------------------------------------------------------------------------------------------------------------------------------------------------------------------------------------------------------------------------------------------------------------------------------------------------------------------------------------------------------------------|
| Protocol Title:                                         | Improving the Mental Health and Well Being of Healthcare Providers During the COVID-19 Pandemic: A Parallel Population Study Investigating the Reduction of Burnout and Enhancement of Well Being through the Transcendental Meditation Technique                                                                                                                                                                                                                                                                                                                                                                                                                                                                                                                                                                                                                                                                                                                                                                                                                                                                                                                                                                                                                                              |
| Protocol Number:                                        | CCCR 01-2020                                                                                                                                                                                                                                                                                                                                                                                                                                                                                                                                                                                                                                                                                                                                                                                                                                                                                                                                                                                                                                                                                                                                                                                                                                                                                   |
| Phase:                                                  | Investigator Initiated Trial (IIT)                                                                                                                                                                                                                                                                                                                                                                                                                                                                                                                                                                                                                                                                                                                                                                                                                                                                                                                                                                                                                                                                                                                                                                                                                                                             |

| Objectives/
Endpoints:                              | 
Primary Endpoints:
 
 
1. Burnout: The Maslach Burnout Inventory (MBI-HSS) for Medical Personnel is used to measure participant burnout [15]. The MBI-HSS is a 22-item inventory with a seven-point response scale, measuring emotional exhaustion (9 items), depersonalization (5 items), and personal accomplishment (8 items). Cronbach's alphas range from .76 to .90 (Iwanicki et al., 1981).
 
2. Insomnia: Insomnia Severity Index (ISI) is a 7-item scale, measuring severity of sleep problems. The ISI has satisfactory internal reliability (Cronbach's alpha=.74) (Bastien et al., 2001).
 
3. Symptom: Brief Symptom Inventory 18 (BSI 18) is a 5-point rating scale used to gather patient-reported data to measure psychological distress and psychiatric disorders in medical and community populations. (Derogatis et al, 2001).
 
4. Well-Being: Warwick Edinburgh Mental Well Being Scale (WEMWBS) is a 14-item scale with 5 response categories, summed to provide a single score. The items are all worded positively and cover both feeling and functioning aspects of mental wellbeing, thereby making the concept more accessible. (Tennant et al, 2006).
 
 |

|                                   |                                                                                                                                                                                                                                                                                                                                                                                                                                                                                                                                                                                                                                                                                                                                                                                                                              |
|-----------------------------------|------------------------------------------------------------------------------------------------------------------------------------------------------------------------------------------------------------------------------------------------------------------------------------------------------------------------------------------------------------------------------------------------------------------------------------------------------------------------------------------------------------------------------------------------------------------------------------------------------------------------------------------------------------------------------------------------------------------------------------------------------------------------------------------------------------------------------|
| Study Design:              | Sixty-five healthcare providers (HCPs) affiliated with the three participating Miami hospitals will be instructed in the Transcendental Meditation Technique as follows: 25 at Baptist Health South Florida Hospital, 25 at Mercy Miami Hospital, and 15 at Encompass Health Rehabilitation Hospital of Miami. A control group of similar numbers of HCPs at each institution will also be recruited, and matched to the best extent possible for gender, age, type of HCP (doctor, nurse, etc.), and work schedule (e.g., days, nights, etc.). Study outcomes will be assessed at baseline, 2 weeks, 1 month, and 3 months' posttest, with change in burnout, insomnia, symptom, and well-being, as measured by the corresponding indexes as the primary outcomes. The total duration of the study period will be 3 months. |
| Inclusion Criteria:        | 
 
1. Fulltime healthcare providers, medical doctors, physician assistants, nurses or other HCPs involved in active patient care or administration of patient care (Hospital Administration).
 
2. 18 years or older.
 
3. Have treated COVID-19 patients or working at locations where COVID-19 patients are being treated.
 
4. Willing and able to complete both baseline and post-testing as noted above.
 
5. If being treated with psychoactive medications, the maintenance of a stable regimen for at least two months before enrollment.
 
6. In the non-control group, willing and able to dedicate the time to learning the Transcendental Meditation technique and practice it twice daily for approximately 20 minutes.
 
       |
| Exclusion Criteria:        | 
 
1. Already instructed in the Transcendental Meditation technique.
 
2. Currently unstable psychiatric symptoms as demonstrated by self-report, medical chart, or psychiatric hospitalizations in the past six months.
 
                                                                                                                                                                                                                                                                                                                                                                                                                                                                                                                                               |
| Investigational Procedure: | Transcendental Meditation Technique                                                                                                                                                                                                                                                                                                                                                                                                                                                                                                                                                                                                                                                                                                                                                                                          |
| Subject Population:        | 25 at Baptist Health South Florida Hospital, 25 at Mercy Miami Hospital, and 15 at Encompass Health Rehabilitation Hospital of Miami. A control group of similar numbers of HCPs at each institution will also be recruited, and matched to the extent possible for gender, age, type of HCP (doctor, nurse, etc.), and work schedule (e.g., days, nights, etc.).                                                                                                                                                                                                                                                                                                                                                                                                                                                            |

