### **3 OBJECTIVES**

#### **3.1 Primary and Secondary Objectives**

##### Primary Endpoints:

1. Burnout: The Maslach Burnout Inventory (MBI-HSS) for Medical Personnel will be used to measure participant burnout [15]. The MBI-HSS is a 22-item inventory with a seven-point response scale, measuring emotional exhaustion (9 items), depersonalization (5 items), and personal accomplishment (8 items). Cronbach's alphas range from .76 to .90 (Iwanicki et al., 1981).
2. Insomnia: Insomnia Severity Index (ISI). The ISI is a 7-item scale, measuring severity of sleep problems. The ISI has satisfactory internal reliability (Cronbach's alpha=.74) (Bastien et al., 2001).
3. Symptom: Brief Symptom Inventory 18 (BSI 18). The BSI 18 is a 5-point rating scale used to gather patient-reported data to measure psychological distress and psychiatric disorders in medical and community populations. (Derogatis et al, 2001).
4. Well-Being: Warwick Edinburgh Mental Well Being Scale (WEMWBS) is a 14-item scale with 5 response categories, summed to provide a single score. The items are all worded positively and cover both feeling and functioning aspects of mental wellbeing, thereby making the concept more accessible. (Tennant et al, 2006).

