#### **3.2 Study Overview**

Sixty-five healthcare providers and hospital administrators (HCPs) affiliated with the three participating Miami hospitals will be instructed in Transcendental Meditation Technique as follows: 25 at Baptist Health South Florida Hospital, 25 at Mercy Miami Hospital, and 15 at Encompass Health Rehabilitation Hospital of Miami. A control group of similar numbers of HCPs at each institution will also be recruited, and matched to the extent possible for gender, age, type of HCP (doctor, nurse, etc.), and work schedule (e.g., days, nights, etc.). Study outcomes will be assessed at baseline, 2 weeks, 1 month, and 3 months posttest, with change in burnout as the primary outcome. The total duration of the study period will be 3 months.

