## **6.2 Schedule of Assessments**

Study outcome measures, The Maslach Burnout Inventory (MBI-HSS) for Medical Personnel, Insomnia Severity Index (ISI), Patient Health Questionnaire (PHQ)-9 depression, Generalized Anxiety Disorder (GAD)-7 and the Warwick-Edinburgh Mental Well-Being Scale (WEMWBS) will be assessed at baseline, 2 weeks, 1 month, and 3 months posttest, (+/- 7 days) with change in burnout as the primary outcome. The measures will either be administered in person or virtually). The total duration of the study period will be 3 months.

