## **7.2 Statistical Methods**

### **7.2.1 General Statistical Methods**

For all primary and secondary outcomes, data will be analyzed using analysis of covariance (ANCOVA). Dependent variable will be change from baseline at three-month post-test, with treatment group as the independent variable, and baseline dependent variable as the covariate. Missing data will be imputed using last observation carried forward (LOCF). Effect sizes will be calculated using Cohen's d: mean differences divided by pooled standard deviation. For the primary outcome, change in total burnout, the significance level will be set at  $p < .05$ , two-tailed. For all secondary outcomes,  $p < .01$ , two-tailed, will be used (to compensate for multiple comparisons).

The primary population for analyses of efficacy data will be ITT population. A supportive analysis will be presented for the PP population if this is significantly different from the ITT population. Continuous data will be summarized by using descriptive statistics (number, mean, median, standard deviation, minimum, and maximum).

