#### **7.2.4 Missing Data**

For each primary efficacy endpoint, missing values will be replaced by the average of all non-missing values at that visit (rounded to an integer value) for the treatment groups being compared. A second confirmatory analysis will treat a missing value as a non-response. There will be no other imputation for missing data in the efficacy analyses.

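### The synopsis and Section 3.1 declare four primary endpoints, while Sections 3.2, 6.2 and 7.2.1 declare burnout alone; the other three outcomes have a significance level only if they are secondary

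*Protocol*

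**What the plan says.** **Four primaries.** The Objectives/Endpoints row of the synopsis numbers burnout, insomnia, symptom and well-being under a primary heading. The Study Design row repeats this: "with change in burnout, insomnia, symptom, and well-being, as measured by the corresponding indexes as the primary outcomes". Section 3.1 carries the same four under its primary heading; the second item begins "Insomnia: Insomnia Severity Index (ISI). The ISI is a 7-item scale, measuring severity of sleep problems". The title of Section 3.1 covers secondary objectives too, but none is listed there.

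**One primary.** Section 3.2 describes the same assessments and concludes "with change in burnout as the primary outcome". Section 6.2 uses the same phrase. Section 7.2.1 states: "For the primary outcome, change in total burnout, the significance level will be set at" .05, two-tailed.

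**The rule for the rest.** For all secondary outcomes Section 7.2.1 sets .01, "two-tailed, will be used (to compensate for multiple comparisons". It does not say which outcomes these are, and neither does any other section.

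**Related wording.** Section 7.2.4 opens "For each primary efficacy endpoint, missing values will be replaced by the average of all non-missing values at that visit", which implies more than one primary. Section 6.2 schedules "Patient Health Questionnaire (PHQ)-9 depression, Generalized Anxiety Disorder (GAD)-7" and omits the BSI 18, although the synopsis and Section 3.1 name the BSI 18 as the symptom measure.

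**The concern.** The set of primary endpoints determines what the trial may claim. Here the synopsis and the objectives section give one set, and the overview, the schedule and the statistical section give another. No text says which prevails, and none says whether four primaries would require success on one, on any, or on all.

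Suppose insomnia gives p = .03 at three months and burnout is not significant. Under Section 7.2.1, with insomnia secondary, that result misses .01. Under the synopsis, insomnia is a primary outcome and the protocol gives no threshold for judging it. Someone who has seen the data could then choose the page that suits the result.

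This is not a detail that a statistical analysis plan would ordinarily supply. The protocol states both versions.

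**Working it through.** **Step 1: set the sections side by side.**

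| Place in protocol | Primary outcome(s) | Level stated there |
|---|---|---|
| Synopsis, Objectives/Endpoints | four | none |
| Synopsis, Study Design | four | none |
| Section 3.1 | four | none |
| Section 3.2 | burnout | none |
| Section 6.2 | burnout | none |
| Section 7.2.1 | total burnout | .05 primary, .01 secondary |
| Section 7.2.4 | refers to each primary endpoint | none |

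Sections 3.2 and the Study Design row are near-copies of one paragraph that differ on exactly this point. Section 3.1 belongs to the body of the protocol and agrees with the synopsis, so the conflict is not just a summary that has fallen behind the main text.

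**Step 2: what level applies to insomnia, symptom and well-being?** If secondary, .01 each. If primary, none, because the .05 in Section 7.2.1 is attached to burnout only.

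**Step 3: type I error for the success claim under each possible rule.** The protocol gives no figure to reproduce here. Inputs are k = 4 outcomes (synopsis, Section 3.1) and the .05 of Section 7.2.1, extended to all four as an assumption.

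- Burnout alone at .05: 5%.
- Any one of four at .05, independent: 1 − (1 − 0.05)^4 = 1 − 0.8145 = 0.1855, or 18.6%. The upper bound is 4 × 0.05 = 20%.
- Any one of four at .05, correlated (simulation of four equally correlated normal statistics, 1,000,000 draws): 17.4% at correlation 0.3, 15.6% at 0.5 and 13.1% at 0.7. These correlations are assumed.
- All four required, each at .05: at most 5%, with no split of alpha needed.
- Any one of four with a Bonferroni split, 0.05/4 = .0125 each, independent: 1 − (1 − 0.0125)^4 = 0.0491, or 4.9%.

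**Step 4: error among the three outcomes if they are secondary.** Each at .01: at most 3 × 0.01 = 0.03; under independence 1 − 0.99^3 = 0.0297.

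**Step 5: what the classification does to power.** Section 7.2.2 gives 65 per group but no effect size, so the standardised effect d is assumed. By the normal approximation, without gain from the baseline covariate, power = Φ(d × √(65/2) − z), where √(65/2) = 5.701 and z = 1.960 at .05 or 2.576 at .01.

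| Assumed d | Power at .05 | Power at .01 |
|---|---|---|
| 0.3 | 40% | 19% |
| 0.5 | 81% | 61% |
| 0.7 | 98% | 92% |

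The noncentral t at d = 0.5 gives 80.8% and 59.4%. If all four were required at .05 and were independent, joint power at d = 0.5 would be about 0.813^4 = 44%. The choice of rule therefore affects both error and power.

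**The case against.** The strongest reply is that Section 7.2.1 already settles the matter. It is the only section that sets significance levels, it names one primary at .05, and it applies a stricter .01 to the rest expressly to allow for multiple comparisons. Sections 3.2 and 6.2 agree with it. On that view the synopsis and Section 3.1 merely use the word primary loosely.

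Much of this stands. Section 7.2.1 is clear when read alone, and it is the sensible text to conform to. But nothing gives it precedence, the synopsis and Section 3.1 are where endpoints are formally declared, and Section 7.2.4 uses wording that suits several primaries. The reply shows which way to amend; it does not remove the conflict.

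Two stronger readings are tempting and are not supported:

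- A reader might infer that the three outcomes are tested at .05 on one page and .01 on another. No page assigns them .05.
- A reader might infer from the synopsis that a win on any one of four scales makes the trial positive, so that the error rate is 13% to 19%. The synopsis states neither a success rule nor a level. Requiring all four fits its wording equally well and would keep the error at or below 5%.

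**Conclusion.** The contradiction is real and should be corrected before any outcome data are examined. Three sections name burnout alone. The synopsis and Section 3.1 name four. The secondary set to which .01 applies is never identified.

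The consequence is an undetermined success criterion, not a demonstrated inflation of error. The false-positive rate is 5% if burnout alone is primary, at most 5% if all four must succeed, and 13.1% to 18.6% only if any one of four at .05 suffices. That range rests on assumed correlations from 0.7 down to zero and on a rule that the protocol does not state. The power figures rest on assumed effects.

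**What to change.** 1. In the synopsis (both the Objectives/Endpoints and Study Design rows) and in Section 3.1, keep change in total burnout as the sole primary endpoint. List insomnia, symptom and well-being under a secondary-endpoints heading, tested at the .01 already stated in Section 7.2.1.
2. Reword Section 7.2.4 so that it refers to a single primary endpoint.
3. Reconcile the symptom instrument between the synopsis and Section 3.1 (BSI 18) and Section 6.2 (PHQ-9 and GAD-7), so that the number of secondary outcomes is fixed.

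**Cost.** Amendment wording only. Three outcomes lose the label of primary.

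**Optional, and not needed for the correction.** The sponsor could test the secondaries only if burnout is significant, using Holm at .05 in place of the flat .01. With three secondaries the first step is 0.05/3 = .0167, and with four it is .0125. With more than five it becomes stricter than .01 (0.05/6 = .0083), so the count must be settled first. The price is that no secondary claim is possible if burnout is not significant, whereas the present rule allows one.
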